### Safety

Because this is an observational study, participation does not involve any risk beyond those associated with the standard care for ARN in Japan. The registry does not contain any information that could identify patients. Each patient is assigned a unique number, and ophthalmologists are responsible for maintaining separate records of patient identities.

### Publication plan

The research findings derived from the registry will primarily be disseminated through peer-reviewed publications. These publications are anticipated to guide clinical practice and support the development of educational materials tailored for patients. Furthermore, the results may be shared at international uveitis conferences, aiming to foster global collaboration and knowledge exchange. Authorship of these publications will be attributed to the research group, which will include participating ophthalmologists and other research staff.

### Statistical analysis

The clinical profile as well as medical and surgical treatment options will be analyzed using descriptive statistics. Biostatisticians and information technology experts ([name] and [name]) will be involved in the planning, execution, and evaluation of the analyses. Multivariate analysis will be performed on changes in visual function over time and complications to identify influencing factors. Best-corrected visual acuity (BCVA) is converted to logarithm of the minimum angle of resolution (logMAR), and visual acuity worse than 0.01 is converted according to previous report [10] as follows: counting fingers, 2.6 logMAR; hand motions, 2.9 logMAR; light perception, 3.1 logMAR; no light perception, 3.4 logMAR. Data of continuous variables are expressed as mean and standard deviation or median and range, depending on normality of data distribution. Non-parametric data will be analyzed by Mann-Whitney U test or Kruskal-Wallis test, while parametric data will be analyzed by Student’s t-test or one-way ANOVA. Categorical variables will be expressed as total number and percentage, and the data will be analyzed by chi-squared test or Fisher’s exact test. The impact of clinical presentations, viral load, diagnostic methods, treatments, and complications will be estimated by odds ratios (ORs) with 95% confidence intervals (CIs). Survival analyses, especially Kaplan-Meier estimates, will be performed to evaluate visual prognosis, progression-free interval, and complications. Time-to-event data for 6, 12, 24, 36 month from the initial visit, the date of diagnosis, and/or vitrectomy were analyzed. A P value less than 0.05 will be considered statistically significant. Multivariate analyses (such as logistic regression analysis, cox proportional hazards regression, generalized estimating equations, and covariance structure analysis) will consider potential confounding variables related to treatment selection and outcomes.

There are primarily four types of machine learning algorithms: random forests, support vector machines, decision trees, and simple Bayesian classifiers. These algorithms are employed to integrate clinical data and image information for analysis purposes. Support vector machines utilize distinct kernels, and each method option and parameter is selected through cross-validation and bootstrap methods. This process aims to identify the combination that optimizes generalization. In contrast to deep learning, which necessitates a substantial number of cases, these machine learning methods ensure a certain level of accuracy even with a limited number of cases. The machine learning algorithms are designed to predict the outcomes of disease onset, diagnosis, treatment, visual function, and clinical decision-making.

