### Sample size, inclusion and exclusion criteria

The goal of the study is to register a total of 500 eyes treated for ARN. The sample size was determined based on an estimation of number of eligible patients from a national uveitis survey in Japan [6]. Patients who meet the international diagnostic criteria for ARN and who have given written consent to participate in the prospective study, including intraocular fluid examination, will be eligible for registration [2,8]. Exclusion criteria are: (1) patient with retinal necrosis caused by pathogens other than HSV-1, HSV-2 or VZV, such as cytomegalovirus (CMV), (2) patient deemed unsuitable for the study by the investigator, and (3) patient in whom related diseases cannot be excluded despite meeting the inclusion criteria. In the case of exclusion from the study, clinical data until the date of consent acquisition will be registered, after which the study will be terminated.

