This registry study has several limitations. Because ARN is a rare disease, a combined retrospective and prospective study design is adopted to maximize data collection. For example, data extracted retrospectively from medical records may be incomplete due to the inherent limitations of retrospective data collection or insufficient data sources. Consequently, retrospective data may be more susceptible to selection bias than data collected prospectively. Furthermore, in this observational study, treatment methods are determined according to the clinical judgment of the ophthalmologists, making it impossible to control for variability. The number of patients included in the study will be small, and the results may not be generalizable to all regions of Japan. Clinical registries provide valuable opportunities to collect data in real-world clinical settings; however, there are inherent limitations to this research approach. As highlighted by Tan et al. [29] in their review of clinical registries in ophthalmology, limitations of clinical registries include potential selection bias due to the voluntary nature of participation by ophthalmologists. Additionally, missing information and typographical errors in data entry are noteworthy concerns. In future review of the registry, the scope of treatment descriptions could be broadened to include specifics such as the antiviral drugs used (e.g., acyclovir and foscarnet), dosages, and administration methods. This protocol will ensure that the field continues to explore innovative approaches. Accordingly, we expect the scope of data collected in the registry to expand as the project gains momentum.

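### Student's t-test and one-way ANOVA are fixed without regard to variances; if unequal-sized groups also differ in spread, the 5% level is not held at any sample size

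*Protocol article*

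**What the plan says.** The Statistical analysis section of the protocol article summarises continuous variables as "mean and standard deviation or median and range, depending on normality of data distribution". It then assigns the tests: "Non-parametric data will be analyzed by Mann-Whitney U test or Kruskal-Wallis test", "while parametric data will be analyzed by Student’s t-test or one-way ANOVA". The significance rule is general: "A P value less than 0.05 will be considered statistically significant".

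The section states no condition on variances and names no unequal-variance version of either parametric test. Normality is tied in so many words to the summary statistics. The split of the tests follows in the next sentence, so reading normality as the selector of the test is a fair inference.

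On group sizes, the section on sample size gives only a total: "The goal of the study is to register a total of 500 eyes treated for ARN". The limitations paragraph of the Discussion says that "treatment methods are determined according to the clinical judgment of the ophthalmologists". No group sizes and no standard deviations appear anywhere.

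**The concern.** Student's t-test and classical one-way ANOVA estimate one common variance from all groups together. In a randomised trial with equal allocation this rarely matters. Here the groups a reader will want to compare (vitrectomy or none, HSV or VZV, one regimen or another) arise from clinical decisions or from the disease, and equal sizes would be a coincidence.

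Unequal spread is also plausible. Groups with a different mix of severity often differ in spread as well as in mean, and the worst eyes are placed at fixed codes on a bounded scale ("counting fingers, 2.6 logMAR; hand motions, 2.9 logMAR; light perception, 3.1 logMAR; no light perception, 3.4 logMAR"). That is reasoning and not evidence, since the article reports no SD.

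When sizes and variances both differ, the pooled standard error is wrong. It is too small if the smaller group is the more variable one, which gives too many false positives. It is too large in the reverse case, which costs power. At stake is whether a published P value below 0.05 from one of these tests means what it says.

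**Working it through.** **The plan's own figure.** The only stated figure on this point is the 0.05 threshold. The 500-eye target comes from a survey-based count of eligible patients and has no effect size, SD or power to reproduce. The check is therefore whether the named tests deliver 0.05 when there is no true difference.

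**Inputs**
- From the article: threshold 0.05 (taken as two-sided; sidedness is not stated) and 500 eyes in total.
- Assumed: a 100 versus 400 split, i.e. shares f1 = 0.2 and f2 = 0.8; SDs s1 (smaller group) and s2 (larger group) as listed below; normal data; eyes treated as independent.

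**Formula (large samples).** Let R be the squared standard error that Student's test uses, divided by the true one:

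R = [(f1·s1² + f2·s2²)(1/f1 + 1/f2)] / [s1²/f1 + s2²/f2]

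Actual false-positive rate = 2·[1 − Φ(1.96·√R)]

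The total N cancels from R. That is why a larger registry does not reduce the error.

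**One case in full, SD 1.0 versus 0.5**
- Numerator: (0.2×1 + 0.8×0.25)(5 + 1.25) = 0.40 × 6.25 = 2.50
- Denominator: 1/0.2 + 0.25/0.8 = 5 + 0.3125 = 5.3125
- R = 2.50/5.3125 = 0.4706; √R = 0.686; 1.96 × 0.686 = 1.345
- Rate = 2·[1 − Φ(1.345)] = 0.179

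**All cases at 100 versus 400.** The simulated columns rest on 40,000 null trials per row for the four unequal rows and 20,000 for the equal-SD row.

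| SD smaller / larger group | R | Formula | Student, simulated | Welch, simulated |
|---|---|---|---|---|
| 1.0 / 0.5 | 2.50/5.3125 = 0.471 | 0.179 | 0.180 | 0.051 |
| 1.0 / 0.7 | 3.70/5.6125 = 0.659 | 0.112 | 0.111 | 0.050 |
| equal | 1 | 0.050 | 0.047 | 0.047 |
| 0.7 / 1.0 | 5.6125/3.70 = 1.517 | 0.016 | 0.016 | 0.050 |
| 0.5 / 1.0 | 5.3125/2.50 = 2.125 | 0.004 | 0.004 | 0.050 |

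**Does N matter?** With a 20:80 split and the smaller group having twice the SD, simulation (20,000 trials each) gives 0.186 at N = 50, 0.177 at N = 100 and 0.176 at N = 500. The limit is 0.179.

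**Which condition does the damage?**
- Unequal sizes, equal variances (20:80): Student 0.053, 0.048 and 0.047 at N = 50, 100 and 500. No harm.
- Equal sizes, unequal variances: Student 0.048 to 0.052. No harm.
- Both unequal: harm, in either direction. Over smaller-group shares of 10% to 30% and SD ratios (smaller/larger) of 0.5 to 2, the formula runs from 0.001 to 0.245. A mild ratio of 1.25 gives 0.101, 0.086 and 0.073 at shares of 10%, 20% and 30%.

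**Three groups (20,000 trials each)**

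| Sizes | SDs | Classical ANOVA | Welch's ANOVA |
|---|---|---|---|
| 350/100/50 | 1/1/1 | 0.048 | 0.048 |
| 350/100/50 | 1/1.5/2 | 0.198 | 0.052 |
| 350/100/50 | 2/1.5/1 | 0.010 | 0.052 |
| 167/167/166 | 1/1.5/2 | 0.056 | 0.049 |

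These calculations describe the parametric tests themselves. They do not model a preceding normality check, so they are not an error rate for the whole two-step procedure.

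**The case against.** Several points stand and limit the finding.

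- **No demonstrated inequality.** A reader might infer that any comparison of unequal-sized groups here will have the wrong false-positive rate. The article does not support that. Unequal size alone does no harm, and the article has no SDs to show that variances differ. The point has to stay conditional.
- **Visual acuity may never reach these tests.** With its fixed codes for very low vision, logMAR acuity may be judged non-normal and go to the rank tests. The point then applies only to variables that pass the normality check. The parametric branch still remains in the plan for those.
- **The objectives do not hang on it.** A reader might also infer that the treatment and prognosis objectives rest on these tests, or that confidence intervals for acuity differences will be wrong. The same section plans multivariable models, odds ratios with confidence intervals, and Kaplan-Meier estimates for those questions, and the only intervals it names are for odds ratios. No primary hypothesis is tied to a t-test.
- **Confounding is the larger problem.** An unadjusted comparison of clinician-selected groups is confounded under Welch's test too.

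One objection does not carry. It says that a condensed article leaves such details to the analysis plan. A variance check left unmentioned would indeed be no finding. But the article names the two pooled-variance tests outright, and an analysis plan that follows it inherits that choice.

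**Conclusion.** The point holds in conditional form. The article commits the parametric branch to two tests that need equal variances, and the only criterion it mentions does not bear on that need. In a registry with groups formed by clinical judgment, unequal sizes are likely. Should variances differ too, the nominal 5% could be anywhere from well under 1% to more than three times 5%. The direction depends on which group is more variable, and the size of the registry gives no protection.

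The percentages rest on assumed splits, assumed SD ratios and normal data. They show what could happen and do not predict what will. Priority is modest: the affected results are unadjusted and sit beside the multivariable models. The change is worth making because the variances cannot be known when the test is chosen, and Welch's versions held the level whether or not the variances differed (0.047 to 0.054 for the t-test and 0.048 to 0.053 for ANOVA over all settings tried).

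**What to change.** In the Statistical analysis section, and in the analysis plan if it repeats the wording, replace Student's t-test with Welch's t-test and one-way ANOVA with Welch's ANOVA for data in the parametric branch. Leave the Mann-Whitney and Kruskal-Wallis tests as they are. Nothing in the calculation concerns non-normal data, so it gives no reason to drop the normality criterion or to move skewed outcomes onto means.

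The cost is one sentence and a negligible loss of power when variances are in fact equal. In a simulated comparison of 100 versus 400 with equal SDs, power was 0.779 for Welch against 0.782 for Student.

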**Methods and design:**

This research is a combined retrospective and prospective, multicenter cohort study of ARN in Japan from 1 April 2014–31 March 2029 (UMIN000056246). The registry has received Japan-wide approval from a national human research ethics committee. The following data will be collected: patient demographics, visual function at the initial visit and 6, 12, 24, and 36 months later, image data, diagnostic methods, virus analysis, indications and timing of vitrectomy, and complications. Customized software and platforms have been designed to permit data collection for a single baseline and multiple follow-up forms.

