ARN is a relatively rare condition, with an annual incidence estimated at 0.63 cases per million population in the United Kingdom [5]. In Japan, ARN accounts for approximately 1.7% of all uveitis cases, underscoring its rarity but significant impact on those affected [6]. In Japan, where ARN has been recognized and studied extensively, the establishment of a nationwide registry represents a significant step toward improving patient care and advancing research in this challenging field. By consolidating data from multiple institutions, the registry will enable large-scale analyses that are not feasible in individual case reports or small case series. A report on the association between initial treatment regimen and retinal detachment rate and visual outcomes in patients with ARN in the American Academy of Ophthalmology IRIS^®^ Registry (Intelligent Research in Sight) has been published [7]. The insights gained from the nationwide registry in Japan will also be instrumental in addressing critical clinical questions, standardizing diagnostic and treatment protocols, and ultimately enhancing the quality of care for patients with ARN.

The primary objectives of the registry are to (1) characterize the clinical features, diagnostic approaches, virus type, and treatment patterns of ARN; (2) assess visual and anatomic outcomes in ARN patients treated with or without surgery; (3) identify visual prognostic factors associated with outcomes; and (4) compare the effectiveness of different treatment regimens. This information would provide valuable insights into ARN epidemiology, clinical features, treatment responses, and long-term outcomes. Such data are essential for developing evidence-based guidelines and optimizing management strategies. The registry would also facilitate collaborative research efforts facilitating the identification of prognostic factors and the evaluation of novel therapeutic approaches.

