### Registered data

The following data will be collected (Table 1): height, weight, age, sex, laterality of ARN, medication history, history of shingles vaccination and herpetic diseases, drinking and smoking history, systemic disease, ocular disease, days from onset of ocular symptoms to first visit, subjective symptoms, best-corrected visual acuity, spherical equivalent, intraocular pressure, axial length, lens status, slit lamp finding (anterior chamber cells and flares, mutton-fat keratic precipitates), presence of vitreous opacity, fundus appearance (extent of yellowish white lesions), presence of retinal holes/tears, status of optic disc (swelling, redness, atrophy), status of the macula (edema, epiretinal membrane, necrosis), optical coherence tomography (OCT) data, treatment (antiviral agents, systemic corticosteroid, photocoagulation), date of surgery, surgical procedure, and complication.

**Table 1 pone.0323822.t001:** List of information collected for J-ARN registry.

Clinical data at initial visit	Treatment method, timing and adverse events	Events and viral copy number	Findings at 6, 12, 24, 36 months after initial visit
Height	Antiviral agents (intravitreal and/or intravenous and/or oral)	Maximum extension of yellow-white lesions	Best-corrected visual acuity
Weight	Systemic corticosteroids	Period until progression of yellow-white lesion stops	Slit lamp findings (AC cells, flare, mutton-fat KPs)
Age	Photocoagulation	Development of retinal detachment	Presence of retinal detachment
Sex	Surgery	Development of proliferative vitreoretinopathy	Presence of optic nerve atrophy
Race	Number of vitrectomy	Recurrence of ARN	Status of the macula (edema, epiretinal membrane, necrosis)
Systemic disease	Intraocular tamponade materials	Development of ARN in the contralateral eye	Presence of proliferative vitreoretinopathy
History of herpetic disease	Intraoperative and postoperative complications	Viral copy number measured during follow-up period	Presence of silicone oil
History of ocular disease			Complications
History of shingles vaccine			
Medication history			
Smoking history			
Days from onset of ocular symptoms to first visit			
Lesion laterality			
Subjective symptoms			
Best-corrected visual acuity			
Spherical equivalent			
Intraocular pressure			
Axial length			
Lens status			
Slit lamp findings (AC cells, flare, mutton-fat KPs)			
Presence of vitreous opacity			
Extent of yellow-white lesions			
Presence of retinal holes/tears			

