Despite aggressive treatment, ARN carries a poor prognosis with high rates of retinal detachment and severe visual impairment [4]. A recent study reported that initial retinal detachment was detected in 2% of ARN patients, increasing to 47% during the follow-up period [13]. However, even after successful retinal reattachment, visual outcome often remains poor due to complications such as maculopathy and optic neuropathy [22]. The registry will track long-term outcomes including visual acuity, retinal detachment rate, complications, and recurrence, providing valuable data to guide future management strategies. Several studies have reported a significant association between the involved zone and the development of retinal detachment [13,23–26]. Furthermore, patients aged 50 years or younger diagnosed with ARN are more likely to develop retinal detachment and more severe ocular inflammation [27]. Several studies have investigated the prognostic factors that influence the clinical outcome of ARN. Choi et al. [28] identified poor initial visual acuity, necrotic retinitis in the central zone, and delayed retinal detachment onset as factors that significantly increase the risk of severe vision loss. Kim et al. [24] found that early diagnosis correlated strongly with better visual outcomes. Butler et al. [25] reported that zone 1 involvement and widespread retinal lesions were associated with worse visual prognosis. The proposed registry will evaluate the association between the development of retinal detachment and various clinical characteristics, and provide valuable data to guide future management strategies.

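### With/without-surgery comparisons: three time origins are offered without saying which serves which, vitrectomy after time zero is not handled, and Table 1 does not show whether detachment preceded surgery

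*Protocol article*

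**What the plan says.** The Introduction makes it a primary objective to "assess visual and anatomic outcomes in ARN patients treated with or without surgery", and another to compare the effectiveness of treatment regimens. The Discussion presents vitrectomy in eyes without detachment as a debated question and the registry as a resource for such controversies.

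In the Statistical analysis section, "Survival analyses, especially Kaplan-Meier estimates, will be performed to evaluate visual prognosis, progression-free interval, and complications". The next sentence gives the origins: "Time-to-event data for 6, 12, 24, 36 month from the initial visit, the date of diagnosis, and/or vitrectomy were analyzed". The impact of treatments is to be estimated by odds ratios with 95% confidence intervals. Multivariate models, among them logistic, Cox and generalized estimating equations, "will consider potential confounding variables related to treatment selection and outcomes".

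On data, the abstract lists "indications and timing of vitrectomy" among the items collected, and the text under Registered data includes the date and type of surgery. Table 1 has rows for surgery, number of vitrectomies, tamponade and surgical complications, under a heading that mentions timing, but no row for indication. Its initial-visit column has holes or tears but not retinal detachment (RD). RD appears as an event, "Development of retinal detachment", with no date named, and as a status at 6, 12, 24 and 36 months.

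**The concern.** Vitrectomy is not a baseline characteristic. It happens some time after the initial visit, and a prophylactic vitrectomy can be done only while the eye is still free of RD. Three difficulties follow for a with/without comparison.

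- **Origin.** An unoperated eye has no vitrectomy date, so that origin cannot serve the comparison. If operated eyes were timed from vitrectomy and the others from the first visit, the groups would have different time zeros.
- **Immortal time.** With a common origin but fixed groups, the RD-free wait before surgery is credited to surgery, and eyes that detach while waiting fall into the unoperated group. Odds ratios share the problem because they ignore when surgery took place.
- **Outcome-defined exposure.** Repair vitrectomy follows RD. If it is counted as surgery in an analysis of RD, the outcome assigns the exposure.

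The last two push in opposite directions. What is at stake is the registry's evidence on prophylactic vitrectomy, which the Publication plan expects to guide practice.

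**Working it through.** There is no effect size or power figure to reproduce: the 500 eyes are a feasibility count. The check is therefore a null model in which vitrectomy has no effect on RD.

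**Input from the documents.** The Discussion cites a study in which "initial retinal detachment was detected in 2% of ARN patients, increasing to 47% during the follow-up period". Applied to 500 eyes (assuming the patient figures carry over to eyes and the 47% includes the 2%): 0.02 × 500 = 10 with RD at the first visit, 0.47 × 500 = 235 by the end, so 225 arise later.

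**Assumed, not in the documents.** In the 47% of eyes that are RD-prone, time to RD is exponential with median 30, 60 or 90 days. Half of all eyes are planned for prophylactic vitrectomy, irrespective of RD-proneness, at an exponential time with median 7, 14 or 30 days; it is done only if RD has not yet occurred. Follow-up is 365 days.

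**Prophylactic vitrectomy, grouped from the initial visit.** The chance that planned surgery precedes RD in an RD-prone eye is w = median(RD) / [median(RD) + median(vitrectomy)]. For medians 30 and 30 (follow-up cut-off negligible), w = 0.50:

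- operated share: 0.5 × (0.53 + 0.47 × 0.50) = 0.3825
- of which RD: 0.5 × 0.47 × 0.50 = 0.1175, a risk of 30.7%
- remaining eyes: (0.47 − 0.1175) / (1 − 0.3825) = 0.3525 / 0.6175 = 57.1%
- risk ratio: 0.307 / 0.571 = 0.54, where the truth is 1

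Simulation of 1,000,000 eyes in each of the nine settings gives risk ratios of 0.54-0.92 and rate ratios of 0.35-0.86.

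**Repair surgery pooled in, 90% of remaining RDs repaired (assumed).** Same setting:

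- repaired: 0.9 × 0.3525 = 0.31725
- RD with surgery: (0.1175 + 0.31725) / (0.3825 + 0.31725) = 0.43475 / 0.69975 = 62%
- RD without: 0.03525 / 0.30025 = 12%

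Over the nine settings: about 60-62% versus 8-12%.

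**Different assumptions, same pattern.**

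- Ever versus never operated, with a prophylactic share of 10-50% and 70-100% of other RD eyes operated: RD in 60-90% of operated versus 0-21% of unoperated eyes. The odds ratio is 5.7 to 57.7, and infinite if every RD eye is operated.
- Prophylactic surgery only, with 40% planned, mean time to RD 6 or 12 weeks, mean time to surgery 1, 2 or 4 weeks, and 2% with RD at the start: odds ratios of 0.45-0.82. Excluding the 2% but keeping fixed groups still leaves 0.47-0.88, so baseline RD is the minor part.

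**Do the remedies work?** In the second set, vitrectomy as a time-dependent exposure in eyes free of RD at the first visit gives rate ratios of 0.99-1.00 in all six scenarios. In the first set, a 30-day landmark among RD-free eyes gives 0.99-1.01 in all nine.

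**Does adjustment help?** Planning of prophylactic surgery is independent of RD risk in these models, so there is no baseline confounding to adjust for. The distortion comes entirely from how eyes are classified.

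**The case against.** The strongest reply is that the protocol nowhere prescribes the faulty comparison. No text fixes eyes as operated or unoperated from the first visit, times the groups from different origins, or pools prophylactic with repair surgery. Cox regression is listed and can take vitrectomy as time-dependent. The vitrectomy origin has a proper use: the Discussion wants to compare tamponade by following vision after vitrectomy, which is a comparison within operated eyes. Much of the remaining detail may sit in an analysis plan that is not shown.

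All of this stands, and it limits the point. A reader might infer that the plan commits the registry to a biased answer on surgery; the documents do not support that.

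A reader might also infer from Table 1 that indication and timing go unrecorded. They do not support that either: the abstract says both are collected, the text lists date of surgery, and Table 1 is not exhaustive (drinking history is in the text but has no row). Kaplan-Meier analysis of complications also presupposes event dates. The finding on indication is a disagreement between abstract and table.

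Nor does fixing visual acuity at months after the initial visit contradict the vitrectomy origin, since that sentence concerns time-to-event data and promises no acuity visits counted from surgery.

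What the reply does not meet is that the article itself names the origins and the effect measure for a primary objective and leaves them unmatched. The promised attention to confounders does not cover immortal time or an exposure defined by the outcome. An analysis plan can choose an origin, but it cannot supply dates or indications that the forms may lack.

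**Conclusion.** The concern holds as a gap in the stated analysis, not as a demonstrated bias. The origins are not tied to comparisons, the later start of vitrectomy is not dealt with, and abstract and Table 1 disagree on indication. Under a null effect, a fixed grouping can give a risk ratio for RD of 0.54-0.92 for prophylactic vitrectomy, and pooling repair surgery can give about 60-62% versus 8-12% RD.

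Only the 47% and 2% come from the documents; the surgical shares, delays and 90% repair are assumed. The ranges show direction and possible size and do not forecast the registry's results. The missing initial-visit RD row is a small part (2% in the cited study, about 10 of 500 eyes). Whether RD came before or after each vitrectomy matters much more.

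**What to change.** - **Origin.** For with/without-surgery comparisons, use one origin for all eyes, either the initial visit or diagnosis, and state it. Keep the vitrectomy origin for comparisons within operated eyes, such as tamponade.
- **Exposure.** Enter vitrectomy as a time-dependent exposure, or use a prespecified landmark among eyes still free of RD. Do not estimate its effect on RD by an odds ratio on ever/never surgery.
- **Type of surgery.** Analyse vitrectomy before any RD separately from vitrectomy for RD. Leave eyes with RD at the initial visit out of incident-RD analyses.
- **Data.** Reconcile Table 1 with the abstract by listing the indication for each vitrectomy, the date of first RD, and RD at the initial visit.

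The cost is revised analysis wording and a few fields that can be taken from charts and operative notes. A landmark drops eyes with very early events; the time-dependent model does not. Recruitment began on 1 April 2025 and records reach back to 2014, so settling the fields early is easier than returning to charts later.
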